## Abstract

**Background:**

Chronic urticaria (CU) is a refractory skin disease with long duration and a high recurrence rate. Acupuncture has been widely used for the treatment of CU in clinical practice in China. However, until now, there has been no appropriately designed randomized controlled trial (RCT) to provide explicit evidence about the effectiveness of acupuncture for the treatment of CU worldwide. Therefore, we plan to conduct a pilot study to explore its effectiveness and safety and determine the feasibility of studying acupuncture in a future, full-scale, RCT of CU.

**Methods/design:**

This randomized, sham-controlled, participant-blinded and assessor-blinded pilot trial is underway in China. A total of 60 participants with CU will be randomly assigned to two groups in a 1:1 ratio: one treated with real acupuncture and the other with sham acupuncture, for 10 sessions over 2 weeks. The experimental group will receive acupuncture on a fixed prescription of acupoints, whereas the control group will receive sham acupuncture, namely minimal acupuncture on non-acupuncture points. The primary outcome will be the urticaria activity score (UAS). The secondary outcomes will include a visual analogue scale (VAS) score for itching intensity, the Dermatology Life Quality Index (DLQI), the Hamilton Depression Scale (HAMD), the Hamilton Anxiety Scale (HAMA), the humoral immunity index, serum total IgE, and adverse events. The UAS, VAS for itching and the DLQI will be conducted at baseline and at 1, 2, 3, and 4 weeks after randomization. The HAMD, HAMA, humoral immunity index, and serum total IgE will be assessed at baseline and at 2 weeks after randomization. Adverse events will be summarized at 1 week and 2 weeks after randomization.

**Discussion:**

The pilot study mainly aims to investigate trial feasibility, and confirm basic information about its effects and safety. Results of this trial will help clarify whether the acupuncture treatment is beneficial for symptom improvement in patients with CU. The finding of this study will provide preliminary evidence on the effectiveness and safety of acupuncture for CU.

**Trial registration:**

Acupuncture-Moxibustion Clinical Trial Registry, AMCTR-ICR-18000190. Registered on 19 June 2018.

**Electronic supplementary material:**

The online version of this article (10.1186/s13063-019-3433-1) contains supplementary material, which is available to authorized users.

## Background

Urticaria is a condition characterized by the development of wheals (hives), angioedema, or both [1]. Angioedema in patients with urticaria is characterized by a sudden, pronounced erythematous or skin-colored swelling of the lower dermis and subcutis or mucous membranes, sometimes pain rather than itch, and slower resolution than that of wheals. Chronic urticaria (CU) is defined on presentation almost daily of transient wheals lasting more than 6 weeks in duration [2, 3]. CU is divided into two types: chronic spontaneous urticaria (CSU) and chronic inducible urticaria (CIU) [1]. CSU refers to the spontaneous appearance of wheals, angioedema or both for > 6 weeks due to known or unknown causes. The signs and symptoms of CIU are triggered by external specific factors, such as a mechanical stimulus (friction, pressure, and vibration), thermal stimulus (cold, heat), aquagenic stimulus (water), and electromagnetic stimulus (solar radiation) [4]. CSU may occur at any age. Recent research showed a female-to-male predominance of 2:1, with a prevalence between 0.5% and 1% [5]. In a meta-analysis [6], the prevalence of CIU was estimated at 13.1–14.9% among patients with CU. CU can induce misery and embarrassment and severely impair the quality of life [7–10], Evidence suggests that patients with CSU can substantially lose productivity at work, school, or in daily activities [11–13]. There are high direct and indirect healthcare costs for treating CU due to the large socioeconomic implications of a 20–30% reduction in performance [14].

The current treatment guidelines [1, 15] and consensus statement [3, 16] recommend a stepwise approach for the complete control of CU symptoms. The European Academy of Allergology and Clinical Immunology, the Global Allergy and Asthma European Network, World Allergy Organization (EAACI/GA^2^LEN/EDF/WAO) guidelines [1] recommend the use of second-generation H1-antihistamines as the first line of treatment. If no response is seen at the regular dose, the dose will be increased up to a 4-fold standard or licensed dose. If there is still no improvement, the guidelines recommend the use of omalizumab and cyclosporine A (CsA) as the third-line treatment. However, all H1-antihistamine treatment options, including the use of higher-than-standard doses, do not have an approved label for the treatment of CU, and many patients experience an inadequate response to most of these drugs [17]. Furthermore, the guidelines do not provide guidance on the choice, dose and duration of alternative treatment options in patients who remain symptomatic despite the use of H1-antihistamines. In addition, although omalizumab and cyclosporine A (CsA) have proven effective [18–20], they are expensive and can impose a serious economic burden on patients. Widespread use will depend on legal and economic factors [21]. Therefore, more and more patients have turned to seek non-pharmacological treatments.

In recent years, acupuncture as an antipruritic measure is used widely in the treatment of skin diseases such as eczema [22], urticaria [23, 24], and neurodermatitis [25]. Some systematic reviews [26, 27] have investigated the effectiveness of acupuncture in the management of CU, but the authors concluded that the clinical results presented in the reviews are tentative and should be interpreted cautiously due to lack of the quality of the studies included. Besides, its scientific basis is still relatively limited owing to a lack of adequate statistical power, insufficient reports, or relevant methodological shortcomings in previous studies. Therefore, we have designed a pilot study with a 2-week observation period to explore its effectiveness and safety and determine the feasibility of studying acupuncture in a future, full-scale, randomized controlled trial (RCT) of CU.

## Method and design

### Study design

This study is a randomized, sham-controlled, patient-assessor blinded, parallel-design clinical trial. Participants will be assigned to the experimental group or the control group for 10 sessions over 2 weeks. The experimental group will be treated with acupuncture in a fixed prescription of acupoints, and the control group will be treated with sham acupuncture, namely minimal acupuncture on non-acupuncture points.

### Setting of the study

This clinical trial will be conducted at the Affiliated Hospital of Chengdu University of Traditional Chinese Medicine. Eligible participants will be randomly assigned to the experimental group (*n* = 30) or the control group (*n* = 30) with a 1:1 ratio. The total observation period will be 5 weeks, including a 1-week baseline period, a 2-week treatment period and a 2-week follow-up period. They will receive 10 sessions of acupuncture or sham acupuncture treatment over 2 weeks (five sessions per week). During the baseline, treatment, and follow-up periods, participants will not be allowed to take any therapeutic medications (e.g., antihistamine, omalizumab, and CsA) for CU. but will be permitted to use antihistamines as necessary (e.g., loratadine, ebastine, and mizolastine) when the wheals and itching are unbearable. The number of wheals, degree of itching, impact on life, and medical history will be recorded in urticaria diaries every day. Assessments will be conducted at baseline and at 1, 2, 3, and 4 weeks after randomization. Figure 1 illustrates the study flowchart. The reporting of this trial is conducted according to the Standard Protocol Items: Recommendations for Intervention Trials (SPIRIT) guidelines [28] (Additional file 1), and the Standards for Reporting Interventions in Clinical Trials of Acupuncture (STRICTA) [29] have been used as frameworks of methodology for designing this protocol (Additional file 2).

**Fig. 1 Fig1:**
[figure not shown]
Flow diagram of the study design

### Recruitment

Sixty patients with CU will be recruited through, but not limited to, reviewing and screening of outpatients in the Affiliated Hospital of Chengdu University of Traditional Chinese Medicine, university media releases, community advertisement including leaflets distributed via regular community health counseling, media campaigns, and network recruitment.

For subject recruitment, three research assistants will go to the department of dermatology in the Affiliated Hospital of Chengdu University of Traditional Chinese Medicine three times a week to identify and invite potentially eligible patients to participate in the study. The patients will be informed of the details of the study such as the objectives, scope, procedure, and potential benefits and risks. The patient will be given a written informed consent form. Patients or their carers will be informed of all the details and potential risks of the study, and the written informed consent form will be signed and witnessed by the research assistant. Oral informed consent may be acceptable if the participants cannot read.

### Inclusion criteria

Eligible participants should conform to EAACI/GA^2^LEN/EDF/WAO guidelines diagnostic criteria for CU and those who meet the following inclusion criteria will be included: (1) the sudden appearance of wheals, angioedema, or both; (2) the occurrence of spontaneous wheals, angioedema, or both for ≥ 6 weeks; (3) suffering from urticaria at least twice a week on average during the previous 6 weeks; (4) aged 18–70 years; (5) antihistamines were not used within 2 weeks before entering the study, and steroids hormone and immunosuppressive drugs were not used within 1 month; (6) agree to participate in this study and provide written informed consent.

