#### Primary outcome

The primary outcome measurement is the urticaria activity score (UAS) [1, 31]. The UAS, which is used to make daily assessments for 1 week, combines daily wheal numbers (0 = none, 1 = < 20 wheals/24 h, 2 = 20–50 wheals/24 h, and 3= > 50 wheals/24 h or large confluent areas of wheals) and pruritus intensity (0 = none, 1 = present but not annoying or troublesome, 2 = troublesome but does not interfere with normal daily activity or sleep, and 3 = severe pruritus, which is sufficiently troublesome to interfere with normal daily activity or sleep). It has a total score of 42 points for 1 week. The primary outcome measurement will be assessed at baseline and at 1, 2, 3, and 4 weeks after randomization.

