The chosen primary outcome is change in the symptom of wheals and angioedema as obtained from the 7-day UAS. Multiple guidelines [1, 15] and a consensus statement [3, 16] recommend the UAS as the main outcome, and the UAS had been widely used as an outcome measure in CU studies. At the same time, assessment of the severity of CU has mainly depended on patient-reported outcomes. The VAS score for itching intensity can directly assess the variations in the severity of subjective symptoms. The available data indicate that urticaria markedly affects both objective functioning and subjective well-being [56–58]. In this trial, we use the DLQI to evaluate quality of life in patients with CU before and after acupuncture treatment. The DLQI is extensively used in evaluating quality of life in skin disease. It is safe and convenient, and also various different language versions of the DLQI are more readily available than the CU Quality of Life Questionnaire (CU-Q2oL) and the Angioedema Quality of Life Questionnaire (AE-QoL). We have obtained the authorization of the Chinese version of DLQI from Finlay [36]. We will also test for correlation between the symptoms of CU and psychiatric disorders by evaluating the HAMD and HAMA in this study. The Humoral immunity index and measurement of serum total IgE will be experimentally assessed to evaluate possible correlation between immunity and the mechanism of the effects of acupuncture on CU.

This trial has its limitations. First of all, this clinical trial will include a small population of participants and will not primarily aim to perform hypothesis testing. For this reason, the results of this study cannot be generalized as basic data for assessing the effect and safety of acupuncture for treatment of CU. Furthermore, because the control group will receive minimal acupuncture, we cannot ignore the possibility of physiological activation caused by needle penetration. The effect of acupuncture will need to be carefully interpreted because the acupuncture points, needling depth, and *de-qi* will be the only differences assessed between groups.

To summarize, this study is funded by the National Key Research and Development Program of the China-Key Project. The study protocol describes the first randomized, patient-blinded and assessor-blinded, sham-controlled trial. The findings of the study will provide feasibility data and basic information about the effect and safety of acupuncture for a future, full-scale RCT in CU.

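### Patients with angioedema and no wheals are eligible and the Discussion says the UAS covers angioedema, but the UAS as defined scores only wheals and itch, so change in angioedema is invisible to the primary outcome

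*Protocol article*

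**What the plan says.** **Eligibility.** In the protocol article, Inclusion criteria, criterion 1 asks for "the sudden appearance of wheals, angioedema, or both" and criterion 2 for "the occurrence of spontaneous wheals, angioedema, or both for ≥ 6 weeks". Criterion 3 sets a frequency, "suffering from urticaria at least twice a week on average during the previous 6 weeks", with no wheal count and no minimum UAS. The word urticaria in criterion 3 does not bring in a wheal requirement, because the Background opens with "Urticaria is a condition characterized by the development of wheals (hives), angioedema, or both". None of the Exclusion criteria removes spontaneous angioedema without wheals.

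**Primary outcome.** The Primary outcome section says that the UAS "combines daily wheal numbers" with pruritus intensity, each graded 0 to 3 per day, for a weekly total of 42.

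**Diary.** The daily diary items listed under Setting of the study are wheals, itching, impact on life and medical history. Angioedema is not among them.

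**Discussion.** The Discussion describes the same outcome differently: "The chosen primary outcome is change in the symptom of wheals and angioedema as obtained from the 7-day UAS". It mentions an angioedema-specific quality-of-life questionnaire only to explain why the DLQI was preferred.

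**The concern.** Three parts of the article disagree about what the primary outcome measures and in whom. Eligibility lets in patients whose only sign is angioedema, the Discussion says their condition is captured, and the instrument has no item for it.

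Two things are at stake. First, a reader of the results could take a change in UAS as evidence about angioedema, for which the scale holds no data. Second, wheal-free patients use at most half of the scale, so they tend to pull the mean difference between the arms towards zero. In a pilot this matters because its estimates feed the next trial. The Sample size estimation section rests the 60 participants partly on how precisely mean and variance will be known, and the Discussion lists primary-outcome data for sizing a larger trial among the purposes of pilot studies.

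**Working it through.** **Step 1. Reproduce the stated maximum.** Inputs from Primary outcome: wheal item 0 to 3, pruritus item 0 to 3, seven days.

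(3 + 3) x 7 = 42, which matches the stated total. No points remain for a third item, so the Discussion's description cannot be right for this scale. It also leaves out itch, which carries half of the points.

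**Step 2. Score range of a patient who never has wheals.**

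- With itch: (0 + 3) x 7 = 21 at most.
- Without itch: (0 + 0) x 7 = 0 in every week.

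The Background says that angioedema brings "sometimes pain rather than itch". The no-itch case can therefore occur, but it is not the rule.

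**Step 3. Effect on the mean difference.** Let D be the mean UAS difference between arms in patients with wheals, k the share of wheal-free patients (taken as equal in both arms), and r the effect in those patients as a fraction of D, between 0 and 1. Then

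overall difference = (1 - k) x D + k x r x D = D x [1 - k x (1 - r)].

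The relative loss is k x (1 - r), which is largest, and equal to k, when r = 0. The documents give neither k nor r, so both are assumed here:

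| Wheal-free patients | k | Loss if r = 0 (upper bound) | Loss if r = 0.5 (effect through itch) |
|---|---|---|---|
| 0 of 60 | 0% | 0% | 0% |
| 3 of 60 | 5% | 5% | 2.5% |
| 6 of 60 | 10% | 10% | 5% |

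**Step 4. What this does to the size of a later trial.** With the SD held constant, the required size grows with 1 / (difference)^2. At the upper bound the factor is 1 / (1 - k)^2:

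- k = 5%: 1 / 0.95^2 = 1.108, about 11% more patients.
- k = 10%: 1 / 0.90^2 = 1.235, about 23% more patients.

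These two figures rest on r = 0 and an unchanged SD, and neither can be checked from the article.

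**The case against.** **The diagnosis may already require wheals.** The Background also says "Chronic urticaria (CU) is defined on presentation almost daily of transient wheals lasting more than 6 weeks in duration", criterion-conforming CU is required, and two dermatology specialists make the diagnosis. This may keep angioedema-only patients few, and k could be 0. It does not settle the matter: the same Background section defines chronic spontaneous urticaria so that angioedema alone suffices, and the operative criteria use that broad wording. The Discussion also foresees angioedema by itself as a complaint, in its remark on rescue medication. If the narrow meaning was intended, the criteria are miswritten.

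**A reader might infer that angioedema-only patients cannot show any effect.** The documents do not support this. Those who itch can move over as many as 21 points of the UAS, and can also change on the itch VAS. Any of them can change on the DLQI. Only a patient with neither wheals nor itch is fixed at 0 on the primary outcome.

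**A reader might also infer that zeros must inflate the spread.** Mixing a share k of zeros into scores with mean m and SD s gives variance (1 - k) x s^2 + k x (1 - k) x m^2. This exceeds s^2 only if (1 - k) x m^2 > s^2. The article gives neither m nor s, so the direction is open.

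**It is a pilot without a power claim, and no angioedema analysis is planned.** This stands, and it limits the consequences. It does not make the Discussion's sentence correct, nor does it remove the bias in an estimate meant for later use.

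**Other remedies exist.** Adding an angioedema measure, or only correcting the Discussion, would also reconcile the passages on what is measured. The latter alone would leave the dilution in place. Whether criterion 3 should demand a minimum severity is a separate question.

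**Conclusion.** The mismatch is certain from the text. The criteria admit angioedema without wheals, the UAS spends all 42 points on wheals and itch, and the Discussion attributes to it a measurement of angioedema that it does not make. Wheal-free patients have a ceiling of 21, or a fixed 0 if they do not itch.

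The size of the numerical effect is not known. The mean UAS difference is diluted by at most the share k of such patients, so 5% and 10% are upper bounds for an assumed 3 or 6 of 60. This bound assumes equal shares in the two arms and an effect in wheal-free patients that lies between none and the full effect. The first assumption holds on average under randomisation. Because stratification is by sex only, a handful of such patients could still fall unevenly between arms of 30. The point deserves correction because it concerns a stated property of the primary outcome and the remedy is cheap. It does not invalidate the trial.

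**What to change.** Reconcile Inclusion criteria, Primary outcome and Discussion:

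1. Reword the Discussion so that the primary outcome is change in wheals and itch from the 7-day UAS, and draw no conclusion about angioedema from it.
2. For patients still to be enrolled, change criteria 1 and 2 to require wheals, with or without angioedema.
3. Keep everyone already randomised in the intention-to-treat set.
4. Add a sensitivity analysis of the primary outcome restricted to patients with a weekly UAS above 0 in the existing 1-week baseline diary. It uses pre-treatment data only, so the comparison between arms stays fair. It removes patients at the floor but not wheal-free patients with itch. It also drops wheal patients who had a quiet baseline week, so it supplements the main analysis and does not replace it.

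The cost is the loss of a few angioedema-only patients and a slight change of eligibility in a trial that the Trial status section reports as ongoing. No new measurement is needed. Items 1, 3 and 4 remain possible even if enrolment is complete.

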### Exclusion criteria

Participants meeting any of the following criteria will be excluded: (1) urticaria is inducible by physical factors (e.g., cold urticaria, delayed pressure urticaria, solar urticaria, heat urticaria, vibratory angioedema); (2) suffering from neurological diseases, mental disorders, immunodeficiency, bleeding disorders; (3) having any serious disease of the heart, liver, kidney, or other organs; (4) those who are pregnant or lactating; (5) patients with severe cognitive impairment; (6) involved in other clinical studies at the same time.

### Withdrawal criteria

Participants meeting any of the following criteria will be withdrawn: (1) participant’s decision to drop out of the study at any time for any reason (2) occurrence of any unexpected serious side effects.

### Blinding

All the participants, outcome assessors, and statisticians will be blinded to treatment allocation during the whole study. Due to the characteristics of the acupuncture clinical trial, it is not possible to blind the acupuncturists to treatment allocation in this trial. Therefore, they will not take part in the assessment procedure. Different treatment groups will receive treatment in different rooms to blind the participants to their treatment allocation. We will indirectly assess the success of blinding by testing credibility after all the treatment sessions [30], and participants will be asked to guess what kind of acupuncture treatment they have received.

### Interventions

In this trial, treatment strategies were developed by consensus with experienced acupuncture practitioners and dermatologists. There are two groups: active acupuncture group and sham acupuncture (superficial non-acupoint acupuncture) group. The location and manipulation of fixed acupoints and non-acupoints are shown in Table 1. Participants in both groups will receive 10 sessions of acupuncture over 2 weeks. Each session will be administered once a day for 5 days consecutively followed by a 2-day rest interval. All acupuncture treatment sessions will be performed by two acupuncturists who are registered Chinese Medicine Practitioners in China and have at least 3 years’ clinical experience in acupuncture practice. Acupuncturists will also receive training before this trial. Contents of the training classes cover the locating of acupoints, needle manipulation skills, and communication skills. The acupuncturists can be admitted to participate in the trial when they can pass the trial training examination.

**Table 1 Tab1:** Locations and manipulations of the acupuncture points selected in this study

Group	Acupoints	Location	Manipulation
Acupoint	Baihui (GV20)	In the head, the front of the forehead is straight up to 5 cun	Subcutaneous insertion to a depth of 0.5–0.8 cun (12.5–20 mm) with manipulation for the *de-qi*
	Shenting (GV24)	In the head, the front of the forehead is straight up to 0.5 cun	Subcutaneous insertion to a depth of 0.5–0.8 cun (12.5–20 mm) with manipulation for the *de-qi*
	Quchi (LI11)	At the elbow, the midpoint of the lateral end of the elbow transverse line and the upper tibia	Puncture perpendicularly to a depth of 1–1.5 cun with manipulation for the *de-qi*
	Zhongwan (CV12)	In the upper abdomen, 4 cun above the umbilicus, the front midline	Puncture perpendicularly to a depth of 1–1.5 cun with manipulation for the *de-qi*
	Tianshu (ST25)	In the abdomen, parallel to the umbilicus, 2 cun in front of the front midline	Puncture perpendicularly to a depth of 1–1.5 cun with manipulation for the *de-qi*
	Xuehai (SP10)	In the anterior region of the femoral, 2 cun above the medial end of the patella and the protuberance of the vastus medialis	Puncture perpendicularly to a depth of 1–1.5 cun with manipulation for the *de-qi*
Non-acupoint	Zusanli (ST36)	Three inches below the patella between the anterior tibia and the extensor digit rum longus muscle	Puncture perpendicularly to a depth of 1–1.5 cun with manipulation for the *de-qi*
	Sanyinjiao (SP6)	On the medial side of the leg, 3 cun above the tip of the medial malleolus, posterior to the medial border of the tibia	Puncture perpendicularly to a depth of 1.0 cun with manipulation for the *de-qi.*
	Non-acupoint 1	Shangxing (GV23, in the head, the front of the forehead is straight up to 1 cun) opens 1 cun. Alternating left and right points	Subcutaneous insertion to a depth of 1–3 mm without manipulation for the *de-qi*
	Non-acupoint 2	Qianding (GV21, in the head, the front of the forehead is straight up to 3.5 cun) opens 1 cun. Alternating left and right points	Subcutaneous insertion to a depth of 1-3 mm without manipulation for *the de-qi*
	Non-acupoint 3	Ulnar side, halfway between the epicondyles medial to the humerus and ulnar side of the wrist	Subcutaneous insertion to a depth of 1–3 mm without manipulation for the *de-qi*
	Non-acupoint 4	Zhongwan (CV12, in the upper abdomen, 4 cun above the umbilicus, the front midline) opens 3 cm, alternating left and right points	Subcutaneous insertion to a depth of 1–3 mm without manipulation for the *de-qi*
Non-acupoint	Non-acupoint 5	Tianshu point (ST25 in the abdomen, parallel to the umbilicus, 2 cun in front of the front midline) opens 1 cun to the outside, the midpoint of the Tianshu and Daheng point (SP15, in the abdomen, parallel to the umbilicus, 4 cun in front of the front midline)	Subcutaneous insertion to a depth of 1–3 mm without manipulation for the *de-qi*
	Non-acupoint 6	On the thigh, the midpoint of the upper iliac spine and the upper outer corner of the sacral floor are opened inward to 2 cm	Subcutaneous insertion to a depth of 1–3 mm without manipulation for the *de-qi*
	Non-acupoint 7	Edge of the tibia 1–2 cm lateral to the Zusanli (ST36) horizontally	Subcutaneous insertion to a depth of 1–3 mm without manipulation for the *de-qi*
	Non-acupoint 8	3 cun above the outer ankle, between the stomach meridian and the gallbladder meridian	Subcutaneous insertion to a depth of 1–3 mm without manipulation for the *de-qi*

